# The effect of postoperative intravenous iron in anaemic, older cardiac surgery patients on disability-free survival (AGE ANEMIA study): study protocol for a multi-centre, double-blind, randomized, placebo-controlled trial

**DOI:** 10.1186/s13063-023-07725-y

**Published:** 2023-10-26

**Keywords:** Randomized controlled trial, Iron deficiency anaemia, Cardiac surgery, Elderly patients, Intravenous iron, Disability

## Abstract

**Background:**

Postoperative anaemia is common in older cardiac surgery patients and often caused by iron deficiency. Anaemia may negatively affect recovery after cardiac surgery. This study aims to determine the efficacy of treatment of postoperative iron deficiency anaemia (IDA) with intravenous iron (IVI) on disability 90 days after cardiac surgery in older patients.

**Methods:**

This is a randomized placebo-controlled double-blind multi-centre trial. In total, 310 patients aged ≥ 70 years with moderate IDA on postoperative day 1 (haemoglobin 85–110 g/L and ferritin concentration < 100 μg/L or iron saturation < 20%) after uncomplicated elective cardiac surgery (aortic valve repair or coronary artery bypass graft surgery) will be included. Patients will be randomly allocated to receive either IVI (ferric derisomaltose) or placebo (sodium chloride 0.9%) on postoperative day 1 in a 1:1 ratio, stratified by centre and type of cardiac surgery. The primary outcome is disability measured by the 12-item World Health Organization Disability Assessment score 2.0 after 90 days. Secondary outcome measures are the number of postoperative red blood cell (RBC) transfusions, change in reticulocyte haemoglobin content (pg) from randomization to hospital discharge, Hb levels at discharge, hospital complications, dyspnoea (assessed with the Rose Dyspnoea Scale) and health-related quality of life (HRQL) (assessed with The Older Persons and Informal Caregivers-Short Form (TOPICS-SF) questionnaire) after 90 days and days alive and out of hospital after 90 days. Lastly, the functional outcomes (e.g. steep ramp or 6-min walk test) and Hb level after 90 days will be assessed as an exploratory endpoint.

**Discussion:**

The results of this study will demonstrate whether early treatment of postoperative IDA with IVI improves disability at 90 days in older cardiac surgery patients.

**Trial registration:**

ClinicalTrials.gov NCT04913649. Registered on June 4, 2021.

**Supplementary Information:**

The online version contains supplementary material available at 10.1186/s13063-023-07725-y.

## Administrative information

Note: The numbers in curly brackets in this protocol refer to the SPIRIT checklist item numbers. The order of the items has been modified to group similar items (see http://www.equator-network.org/reporting-guidelines/spirit-2013-statement-defining-standard-protocol-items-for-clinical-trials/).

## Introduction

### Background and rationale {6a}

Postoperative anaemia occurs in 80–90% of cardiac surgery patients due to blood loss, haemodilution, inflammation-induced blunted erythropoiesis and pre-existing anaemia [1]. The default treatment of postoperative anaemia is allogenic blood transfusion [2]. However, because of the associated risks with adverse outcomes, transfusion thresholds have become more restrictive over the years. This results in patients being discharged after surgery with low haemoglobin (Hb) levels [3]. In older non-surgical patients, anaemia is associated with disability, diminished physical performance and lower muscle strength [4, 5]. Furthermore, anaemic patients frequently suffer from fatigue, lethargy and dyspnoea [6, 7]. The negative effects of anaemia may impair physical functioning after cardiac surgery, which is a prognostic marker for mortality and readmission [8]. Elderly patients tolerate anaemia poorly and are at increased risk for poor functional outcomes due to frailty and multimorbidity [3, 9–11]. Especially in these patients, postoperative anaemia could impair postsurgical recovery, daily functioning and health-related quality of life (HRQL) [3, 9–11].

Although the underlying causes of postoperative anaemia are multifactorial, (functional) iron deficiency is present in the majority of the anaemic patients [1, 3, 12]. Oral iron supplementation is a recommended approach to treat iron deficiency anaemia (IDA), but treatment can take as long as 6 months to fully normalize Hb levels. Also, in post-surgical patients, the residual iron supplement remains largely unabsorbed in the digestive tract, leading to gastrointestinal side effects. As an alternative, intravenous iron (IVI) has yielded promising results in a number of surgical settings, and the positive effect of IVI on Hb levels remained present up to 6 months after treatment, although the evidence remains weak for cardiac surgery [12–17]. This suggests that IVI treatment might especially be beneficial in the recovery period. Prior studies on postoperative anaemia and functional outcome are scarce. In anaemic, nonsurgical patients with heart failure, treatment with IVI was proven beneficial regarding hospitalizations, quality of life scores and exercise capacity. It is plausible that anaemia correction with IVI can improve functional outcomes following cardiac surgery, especially in elderly patients. However, the effect of treatment of IDA on functional status after cardiac surgery in older patients has not yet been evaluated. We hypothesize that postoperative treatment of IDA with IVI improves functional outcomes in older patients after cardiac surgery.

### Objectives {7}

The primary objective is to evaluate the effect of early treatment of postoperative IDA with intravenous iron (IVI) compared to placebo on disability after 90 days in older patients after elective cardiac surgery. The secondary objectives are to evaluate whether administration of postoperative IVI improves patient-reported outcome measures (PROMs) related to dyspnoea symptoms and health-related quality of life (HRQL) after 90 days. Additionally, we will investigate the effect of treatment with IVI on postoperative RBC transfusions, change in reticulocyte haemoglobin content (pg) during hospitalization, Hb levels at discharge, hospital complications and days alive and out of hospital after 90 days. Lastly, functional outcomes (e.g. steep ramp or 6-min walk test) and Hb levels after 90 days will be assessed as an exploratory endpoint.

### Trial design {8}

This is a randomized placebo-controlled double-blind multi-centre superiority trial with two parallel groups in which IVI is compared to a placebo. The patient allocation ratio is 1:1, stratified by centre and type of cardiac surgery.

## Methods: participants, interventions and outcomes

### Study setting {9}

This study is initiated in two large community hospitals in the Netherlands (St. Antonius Hospital, Nieuwegein, and Amphia Hospital, Breda). Patients are preoperatively recruited and eligible if they meet the criteria as defined below.

Primary inclusion criteria:

In order to be eligible to participate in this study, a subject must meet all of the following criteria:Age ≥ 70 years and mentally competentElective AVR or CABG surgery (including AVR or CABG surgery combined with rhythm surgery, i.e. maze, pulmonary vein isolation and left atrial appendage closure)

Primary exclusion criteria:

A potential subject who meets any of the following criteria will be excluded from participation in this study:Medical history of iron overload/haemochromatosisMedical history of liver cirrhosis or ALT/AST serum concentrations > 3 times the reference value (female patients: ALT > 120, AST > 105 U/L, male patients: ALT > 150, AST > 135 U/L)Renal failure (eGFR < 15 mL/min/1.73 m^2^)Recent treatment with IVI (< 12 weeks prior to surgery date)Serious or severe allergic reaction to IVI in medical historySevere asthma or eczema in medical history (atopic constitution)

Definitive eligibility is assessed at postoperative day (POD) 1 based on the criteria below:

Moderate postoperative IDA, defined as:Hb between 85 and 110 g/L(TSAT) < 20%Meeting the criteria for discharge from ICU to general ward (uncomplicated surgery), defined as:No inotropic agents or ventilation at the time of final inclusion (POD 1)Expected discharge to a general ward at POD 1

### Who will take informed consent? {26a}

Eligible patients will be informed about this study by means of a conversation with the anaesthesiologist and an information brochure. The aims of the study, the methods used and the potential risks and benefits for the patient are described in this brochure. Patients are given the opportunity to ask questions about the study during and after visiting the outpatient clinic. After a reasonable term, the patients will be contacted by telephone for informed consent by a member of the research team. At hospital admission, informed consent will be signed by the patient and study personnel.

### Additional consent provisions for collection and use of participant data and biological specimens {26b}

Not applicable. No biological specimens or additional data will be collected.

## Interventions

### Explanation for the choice of comparators {6b}

The control group will receive 250-mL sodium chloride (NaCl) 0.9% as an infusion drip (placebo). This will ensure an optimal comparison with the treatment group.

### Intervention description {11a}

The patient will undergo surgery according to standard practice. Postoperatively, patients will be admitted to the ICU (standard care). On the first postoperative morning, the iron status will be assessed from a routine blood sample in patients with uncomplicated surgery who meet the ICU discharge criteria. Patients with IDA will be randomly allocated to either the treatment group or the placebo group. Patients randomized to the treatment arm will be administered a single dose of ferric derisomaltose (Monofer®) 100 mg/mL solution for infusion in 60 min. The method of administration and dosage of the investigational medication are standard treatment. The ferric derisomaltose dose will be calculated for each patient depending on ideal body weight (20 mg/kg) and diluted in 250 mL NaCl 0.9%. The maximum ferric derisomaltose dose is 2000 mg. The placebo group will receive 250 mL NaCl 0.9% w/v in 60 min. The study medication will be administered before ICU discharge by a trained nurse. Vital signs of the patient will be monitored during administration of the study medication and for 30 min afterwards. The study medication will be administered through a central venous catheter which is placed after induction of anaesthesia before the start of surgery (standard care). No additional venous access is required to administer the study medication. Both the infusion bag and the infusion line are light-protected (Codan®). Participation in the trial will not delay ICU discharge.

### Criteria for discontinuing or modifying allocated interventions {11b}

Patients can leave the study at any time for any reason without any consequences. The patient data that have been collected up to that moment will be included in the analysis. Acute severe hypersensitivity reactions may occur with parenteral iron preparations. They usually occur within the first few minutes of administration and are generally characterized by the sudden onset of respiratory difficulty and/or cardiovascular collapse. In the case of signs/symptoms of acute hypersensitivity reactions or anaphylactic shock (frequency is rare: incidence is less than 0.1%), the intervention will be discontinued and the patient will be excluded from the study. An excluded patient will be replaced by a new patient. Hypersensitivity reactions and anaphylactic shock will be treated according to standard protocol. In addition, a Fishbane reaction may occur in patients treated with IVI. A Fishbane reaction is characterized by flushing of the face, acute chest and/or back pain and tightness in the chest, which is sometimes accompanied by dyspnoea. This may mimic the early symptoms of an anaphylactic reaction. However, they disappear shortly after administration is discontinued. Approximately 15 min after the symptoms have disappeared, the infusion will be restarted with a 50% lower infusion rate. A Fishbane reaction typically does not reoccur if IVI administration is restarted at a lower infusion rate and is therefore not necessarily a reason to exclude the patient from the study.

In accordance to Sect. 10, subsection 4, of the Dutch Medical Research with Human Subjects Law (WMO (Wet medisch-wetenschappelijk onderzoek met mensen)), the sponsor (St. Antonius Hospital) should suspend the study if there are sufficient grounds that continuation of the study will jeopardize subject health or safety. However, ferric derisomaltose is an IV therapy approved by the EMA. The EMA concluded that the benefit-risk balance of intravenous iron is favourable in the treatment of iron deficiency when used under their current indications. In this study, ferric derisomaltose will be used within its approved indication, and subsequently, the risks associated with the treatment are considered low.

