## Statistical methods

### Statistical methods for primary and secondary outcomes {20a}

Data will be analysed using R statistics (version 3.5.1—© 2018–07-02, R, Inc., for Windows). Descriptive statistics will be calculated for all study parameters. Continuous data will be described as mean (+ standard deviation) and median (+ interquartile range) for normally and non-normally distributed data, respectively. Categorical variables will be described as numbers and percentages. The effect of IVI therapy on the primary and secondary endpoints will be analysed with ANCOVA and logistic regression analysis. All analyses are performed according to the intention-to-treat principle. Two-sided *P* values of 0.05 or less will be considered statistically significant.

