### Methods in analysis to handle protocol non-adherence and any statistical methods to handle missing data {20c}

We intend to test superiority using an intention-to-treat analysis. Thus, all randomized participants, regardless of protocol adherence, as randomized to treatment allocation will be included in the analysis. Missing data will be reduced to a minimum, as described above. However, in case of missing data, these will be compared between the two groups, and imputed using multiple imputations.

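### Excluding and replacing patients who have a hypersensitivity reaction after randomisation contradicts the stated intention-to-treat analysis

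*Protocol article*

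**What the plan says.** All references are to the protocol article.

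- **Order of events.** Intervention description {11a} has iron status assessed on the first postoperative morning, and then "Patients with IDA will be randomly allocated to either the treatment group or the placebo group". The infusion follows. For the comparator, "The placebo group will receive 250 mL NaCl 0.9% w/v in 60 min".
- **Exclusion rule.** Criteria for discontinuing or modifying allocated interventions {11b} introduces the risk with "Acute severe hypersensitivity reactions may occur with parenteral iron preparations". It then sets the rule for patients with signs or symptoms of such a reaction or of anaphylactic shock: "the intervention will be discontinued and the patient will be excluded from the study. An excluded patient will be replaced by a new patient".
- **Analysis rule.** Statistical methods {20a}: "All analyses are performed according to the intention-to-treat principle". Section {20c}, on non-adherence and missing data, is more specific: "all randomized participants, regardless of protocol adherence, as randomized to treatment allocation will be included in the analysis". It adds that missing data will be multiply imputed.
- **Related text.** {11b} also says that the data gathered so far will be used for patients who choose to leave. It describes the Fishbane reaction, of which it says "This may mimic the early symptoms of an anaphylactic reaction", and which need not lead to exclusion.

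**The concern.** An infusion reaction can only happen after randomisation. A rule that takes the patient out of the study because of it, and enrols someone else instead, makes the analysed set differ from the randomised set. The intention-to-treat statements promise that this will not happen.

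The event that triggers removal is not neutral between arms. The protocol attributes it to iron, and the other arm receives saline. Removal would therefore depend largely on the allocated treatment. If patients who react do worse over the next 90 days, leaving them out would make the iron arm look better than it is on disability, on days alive and out of hospital, and on complications. The rule also gives sites and analysts incompatible instructions, which would have to be settled after an event had occurred.

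**Working it through.** **1. The plan's own figure.** Sample size {14} uses a difference of 5 points, SD 15, two-sided 5% and 80% power:

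n per arm = 2 × (1.960 + 0.842)² × 15² / 5² = 2 × 7.85 × 9 = 141.3, so 142, as stated. Two arms need 284. The planned total is 310, or 155 per arm, which leaves 310 − 284 = 26 patients for loss to follow-up.

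**2. The two rules side by side.** Take a patient randomised to iron who reacts during the infusion.

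- Under {11b} the patient is out of the study and a new patient takes the place.
- Under {20a} and {20c} the patient is analysed in the iron arm whatever happened to the infusion.

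Two other sentences might reconcile these, but neither does. The sentence on data gathered so far concerns patients who leave by choice. Even if it were extended to excluded patients, a reaction on postoperative day 1 leaves no day-90 score. Multiple imputation could supply a value only if the patient stayed in the analysis set, and it would then stand in for a score that could have been observed. The article nowhere says that an excluded and replaced patient is followed to day 90 or kept in the analysis.

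**3. How many patients.** {11b} gives an incidence below 0.1%. With 155 iron patients:

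- Expected number: at most 155 × 0.001 = 0.155, about 0.16.
- Chance of at least one: at most 1 − 0.999^155 = 0.144, about 14%.

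**4. How much each could matter.** With n patients in the arm, dropping one who would score x while the others average m shifts the arm mean by (x − m)/n. Replacing that patient with one who scores m gives the same shift. Outcomes {12} scores death as 100, and {14} gives an expected mean of 12.

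- Patient who would score 100: (100 − 12)/155 = 0.57 points, or 0.57/5 = 11% of the target difference.
- Patient 15 points worse than the others: 15/155 = 0.10 points.
- Expected shift if every excluded patient would have scored 100: 0.155 × 88/155 = 0.09 points, about 2% of the target.

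**The case against.** The strongest reply is that this almost never happens. At the protocol's own incidence the most likely number of exclusions is zero, and even the worst-case expected shift is below a tenth of a point. That stands, and it sets the severity. It does not reconcile the two rules.

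Several stronger readings are tempting, but the documents do not support them.

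- **Many more patients would be excluded.** The trigger covers signs and symptoms, and a Fishbane reaction can resemble one. At an assumed 0.5% to 2%, the expected number would be 155 × 0.005 = 0.8 to 155 × 0.02 = 3.1, with a 54% to 96% chance of at least one. No such rate is in the documents. {11b} attaches its figure of below 0.1% to the whole trigger, although the data monitoring section {21a} ties the same figure to anaphylactic reactions. {11b} also says that a Fishbane reaction need not lead to exclusion.
- **All exclusions would be in the iron arm.** A placebo patient with sudden breathing difficulty or collapse on the day after cardiac surgery could meet the wording too. Mainly is supported; only is not.
- **The bias runs in favour of iron.** Nothing in the article says that patients who react have worse day-90 scores. If their outcomes are average, there is no bias in the mean.
- **Safety data are thrown away.** Adverse event reporting {22} records all adverse events, so the reaction itself is captured. What is at risk is the patient's 90-day outcome.
- **Replacement breaks the blind or the randomisation list.** The article does not say that the replacement goes to the vacated arm; it may simply be one more enrolment. Implementation {16c} has staff who are not blinded do the allocating.

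**Conclusion.** The contradiction is real and is visible in the article itself: {11b} removes and replaces a randomised patient, while {20a} and {20c} keep every one. It is not a detail left to an analysis plan, because both rules are stated.

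This is a should-fix point. It is an error of principle with a probably negligible numerical effect, and it does not threaten power. That judgement rests on the stated incidence applying to the trigger as written and on about 155 patients in the iron arm. The 0.57-point figure further assumes that the excluded patient would have scored 100 and that the others average 12. The direction of any bias is conditional on those patients faring worse.

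**What to change.** Reconcile {11b} with {20a} and {20c} through a narrow edit:

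- In {11b}, remove only the clause that excludes the patient from the study and the sentence that follows it on replacement.
- Add in their place: *A patient in whom this occurs is followed to day 90, subject to consent, and is analysed in the allocated arm. A missing day-90 score is handled by the planned multiple imputation. No randomised patient is removed from the analysis or replaced.*

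The wording on discontinuing the intervention and treating the reaction stays untouched. Deleting the whole exclusion sentence would also delete the rule on discontinuation, which is a clinical matter outside this point.

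The cost is a short amendment. The total stays at 310, since the 26 patients above the required 284 easily cover the fraction of a patient expected. Trial status reports thirty patients included at the time of writing, so most of recruitment was still to come. If anyone has already been excluded under this rule, the report should say so and, subject to consent, that patient should be followed and analysed as allocated.

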### Strategies to improve adherence to interventions {11c}

Apart from the intervention at POD 1, patients will receive standard care during hospital admission. Prior to the start of the trial, nurses and physicians at the ICU have received information about the study protocol and were trained in the administration of IVI infusion and handling of infusion reactions, which will improve protocol adherence.

### Relevant concomitant care permitted or prohibited during the trial {11d}

Not applicable. No relevant concomitant care is prohibited during the trial.

### Provisions for post-trial care {30}

The sponsor has a trial subject insurance for patients participating in the study. The insurance provides coverage for study-related damage, which becomes apparent during or within 4 years after the end of the study. Participants receive information on the trial subject insurance in the study information brochure.

### Outcomes {12}

The primary endpoint is the difference in median disability scores as measured by the 12-item World Health Organization Disability Assessment score 2.0 (12-item WHODAS 2.0) 90 days after elective cardiac surgery, between the two treatment arms. The 12-item WHODAS 2.0 is a validated questionnaire for the assessment of postsurgical disability in the following domains: communication, mobility, self-care, interacting with other people, taking care of housework and participating in the community. A disability score is calculated ranging from 0% (no disability) to 100% (fully disabled, including death). The difference in the proportion of patients with new disability between the two treatment arms is a secondary endpoint, defined as an increase in the 12-item WHODAS 2.0 score ≥ 5% at day 90 compared to the preoperative assessment (baseline) [18]. Other secondary endpoints are the difference in the median number of red blood cell (RBC) transfusion administered during hospital stay, the median change in reticulocyte haemoglobin content from POD 1 to hospital discharge, median Hb levels at discharge, proportion of in-hospital complications, median days alive and out of the hospital after 90 days, median score regarding dyspnoea symptoms after 90 days (assessed with the Rose Dyspnoea Scale (RDS)) and median HRQL scores (assessed with The Older Persons and Informal Caregivers-Short Form (TOPICS-SF) questionnaire) after 90 days. Lastly, we will consider functional outcomes (e.g. steep ramp or 6-min walk test) and median Hb levels after 90 days, as exploratory endpoints.

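### The red-cell transfusion endpoint has two different counting windows, and both include units given before randomisation on POD 1, which dilutes any effect of the study infusion

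*Protocol article*

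**What the plan says.** Three sections of the protocol article name the endpoint, with two different windows:

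- Outcomes {12}: "the difference in the median number of red blood cell (RBC) transfusion administered during hospital stay".
- Abstract, Methods: "the number of postoperative red blood cell (RBC) transfusions".
- Objectives {7}: "the effect of treatment with IVI on postoperative RBC transfusions".

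Treatment starts later than either window. Intervention description {11a} states "On the first postoperative morning, the iron status will be assessed from a routine blood sample", and allocation follows that result. The abstract likewise places iron or "placebo (sodium chloride 0.9%) on postoperative day 1 in a 1:1 ratio". In Participant timeline {13}, admission, consent and baseline come before surgery, so the hospital stay includes the operation and the first ICU night.

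The same sentence of {12} does tie another in-hospital endpoint to the day of treatment: "the median change in reticulocyte haemoglobin content from POD 1 to hospital discharge".

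Statistical methods {20a} summarises the transfusion count descriptively, compares arms by t test or Wilcoxon rank sum test according to the distribution, and evaluates secondary outcomes with ANCOVA. The article gives no transfusion rate.

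**The concern.** A unit given in theatre, or in the ICU before the infusion, cannot be caused or prevented by the infusion. Counting it adds the same expected number to each arm. The absolute difference in mean units stays the same, the ratio moves towards 1, and variance rises, so a real effect on later transfusion is harder to see.

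The two windows also do not give the same count. The hospital-stay window includes intraoperative units. The postoperative window leaves those out but keeps units given between the end of surgery and randomisation. Two analysts following different sections would report different endpoints.

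A second, conditional issue concerns the summary measure. If fewer than half of the patients in each arm are transfused in the counting window, both medians are 0 and their difference carries no information on effect size.

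**Working it through.** **Figures in the plan.** There is none for transfusion. The only sample size is for the primary endpoint (difference 5, SD 15, two-sided 5%, power 80%), and it reproduces: n = 2 × (1.960 + 0.842)² × 15² / 5² = 141.3, rounded up to 142 per arm. The planned total of 310 gives 155 per arm. These arm sizes are used below. Every transfusion rate is an assumption.

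**Step 1: which units each window counts.**

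| Window | In theatre | End of surgery to randomisation | Randomisation to discharge |
|---|---|---|---|
| Outcomes {12} | yes | yes | yes |
| Abstract and Objectives {7} | no | yes | yes |
| Units the infusion can affect | no | no | yes |

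**Step 2: dilution of the ratio.** Let m0 be mean units before randomisation (both arms), m1 mean units afterwards in the control arm, and r the true ratio afterwards. The observed ratio is (m0 + r·m1) / (m0 + m1). With m1 = 0.5 and r = 0.5:

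- m0 = 0: 0.25 / 0.50 = 0.50
- m0 = 0.25: 0.50 / 0.75 = 0.67
- m0 = 0.5: 0.75 / 1.00 = 0.75
- m0 = 1.0: 1.25 / 1.50 = 0.83
- m0 = 1.5: 1.75 / 2.00 = 0.88

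**Step 3: power.** Assumptions: 155 per arm; negative binomial counts, independent before and after randomisation; later means 0.5 and 0.25 with dispersion 0.6; earlier counts with dispersion 0.8. Wilcoxon power from 3,000 simulated trials, and from a repeat with 1,500:

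| Mean units before randomisation | 3,000 trials | 1,500 trials |
|---|---|---|
| 0 (count from randomisation) | 72% | 73% |
| 0.25 | not run | 48% |
| 0.5 | 38% | 37% |
| 1.0 | 26% | 26% |
| 1.5 | 19% | 21% |

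A separate set used 142 per arm, dispersion 0.5, m0 and m1 each from 0.3 to 1.0, r = 0.5 or 0.7, and 1,000 trials per case. With m0 = m1 = 0.6 and r = 0.5, power fell from 68% to 36%. Over the 18 cases the observed ratio ranged from 0.62 to 0.93, and power was lower with the wider window every time. The smallest loss was 29% to 24% (m0 = 0.3, m1 = 1.0, r = 0.7).

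**Step 4: the median.** With 142 per arm, a sample median is 0 when at least 72 patients have no units. If a proportion p is transfused in control and 0.7p with iron, the probability that both medians are 0 is P(X ≥ 72) × P(Y ≥ 72), where X is binomial(142, 1 − p) and Y is binomial(142, 1 − 0.7p):

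| Control proportion transfused | Both medians 0 |
|---|---|
| 10–30% | 1.00 |
| 40% | 0.99 |
| 45% | 0.87 |
| 50% | 0.47 |
| 55% | 0.10 |
| 60% | 0.006 |

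In the wider window a zero median is less likely. Under the Step 3 parameters, the share of patients with no units at all is 47% in control and 55% with iron at m0 = 0.5, and 36% and 42% at m0 = 1.0.

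**The case against.** The best defence is that the three sections, read together, mean postoperative units up to discharge. Intraoperative units then drop out, and only the interval from the end of surgery to POD 1 remains, in patients selected for an uncomplicated course. {18a} also says that outcome definitions are held in a data management manual and codebook, which are not shown and may fix the start time. This narrows the problem but does not remove it: {12} still states the wider window, and the narrower one still starts before randomisation. Brevity is a weak explanation when the same sentence gives the reticulocyte endpoint a POD 1 start.

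The sizes in the working are fairly criticised as illustrations. The documents give no rate, no split before and after randomisation, and no expected effect on transfusion. Means of 1.0 or more before randomisation are least plausible under the postoperative reading.

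A reader might infer more in three ways, and the documents do not support it:

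- **That the median comparison will be uninformative.** This needs a transfusion rate that the protocol does not state, and zero medians are mainly a risk in the window from randomisation, not in the one now written. {20a} also plans a rank test, which had about 72% power in simulations where both medians were always 0.
- **That the result is biased.** Units given before randomisation are balanced in expectation.
- **That in-hospital complications are equally affected.** Their start time is not stated either, but eligibility already requires readiness for ICU discharge on POD 1, and no size can be given.

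**Conclusion.** The point holds for the counting window. The sections disagree, and each window as written includes units that the infusion cannot influence. The direction, a ratio closer to 1 and lower power, was the same in every scenario tried. The size depends on assumed rates: with about 0.5 units per patient before and after randomisation and a halving by iron afterwards, the ratio goes from 0.50 to 0.75 and Wilcoxon power from roughly 70% to under 40%. With few units before randomisation the loss is small.

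The concern about medians is secondary and conditional. It matters if clearly fewer than half of the patients are transfused after randomisation. That is plausible given an entry haemoglobin of 85–110 g/L and the restrictive practice described in the background, but it is not documented. This is one of several secondary endpoints; the primary analysis and the sample size do not depend on it.

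**What to change.** Use one definition in the abstract, Objectives {7} and Outcomes {12}: number of red-cell units from randomisation on POD 1 to hospital discharge. Starting at randomisation suits the intention-to-treat analysis, because the time exists for every randomised patient. Record units given between admission and randomisation as a baseline variable, by arm.

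Keep the planned Wilcoxon test, and report beside it the proportion of patients transfused or a ratio of mean units with a 95% confidence interval, so that the effect estimate does not rest on a difference in medians. A particular count model is a matter for the analysis plan and is not required here.

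The cost is a change of wording and a small extra effort to extract the time of each transfusion from the electronic patient records that {18a} already uses. No visits, patients or blood samples are added.
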